### Allocation

We will cluster randomize by PACT team to prevent a team from having patients in both treatment groups and reduce contamination. Prior to initiating enrollment, the lead investigator ([name]) will assign PACTs to notification-plus-coordination or notification-only groups, using lists of computer-generated random numbers in a 1:1 ratio, with separate lists for the Bronx VA and Indianapolis VA, in order to maintain balance in groups within each study site. There are 25 primary care PACTs in the Bronx and 41 in Indianapolis, and each PACT will keep its group assignment for the duration of the study. In Phase 1, enrolled patients will be assigned to notification-plus-coordination or notification-only groups according to their assigned PACT team.

### Data collection methods

We will collect data on veterans using a variety of methods. At baseline as well as 30 days following an acute care event, we will capture data from the Veteran or a caregiver using a questionnaire administered by a trained Research Assistant. The questions asked will pertain to a veteran’s demographics, high risk medications, functional status, and mental health status. High risk medication use will be assessed using a series of questions asking whether the veteran takes blood thinners, medicine for diabetes, pain medications, sleep medications, or mental health medications. Functional status will be assessed using the Katz Activities of Daily Living (ADL) [33] as well as the Lawton Instrumental ADL [34] screeners. Mental health status will be assessed using the Short Portable Mental Status Questionnaire (SPMSQ) [29].

At 30 days following an acute care event, we will also ask questions about the acute care event, care transitions following the acute care event, and perceptions of HIE. veterans will be asked to recall the reason for their acute care event as well as the reason why they chose to use a non-VHA hospital. Care transitions will be assessed using a validated measure of condition self-knowledge and transitional care quality from the patient’s perspective [28]. Perceptions of HIE will ascertained using questions that ask veterans how they feel about their health information being shared electronically between their VHA and non-VHA providers. We will also ask whether they feel that sharing information electronically had any effect on the quality of care they received.

At 90 days following a non-VHA acute care event, trained RAs will extract data from the veteran’s electronic medical records to ascertain primary outcomes, including readmissions following the acute care event as well as health status. The medical records will be obtained from the VHA central data warehouse as well as the Bronx RHIO and Indiana HIE. This will ensure broad capture of data from all available sources pertaining to the non-VHA event as well as follow up within the VHA health system. The RAs will use a standardized template for electronic chart review. Before beginning record reviews and periodically during the study, the research staff will code 5–10 previously coded medical records. We will retrain if accuracy per chart is less than 95%.

During the intervention period, we will interview PACT team members about their experiences with the event notifications they receive in the EHR. We will interview doctors, nurses, medical assistants, and other clinical staff regarding whether they have noticed the alerts and what steps they take following an alert. We will further ask team members about their perceptions of the alerts, such as whether they are barriers or facilitators in care coordination processes. Interviews will further provide an opportunity to capture feedback on the notifications as well as the processes in the VHA that could enable or prevent widespread implementation of event notifications across the VHA health system. These interviews will be conducted using a semi-structured interview guide to be developed by the investigators and influenced strongly by the Consolidated Framework for Implementation Research (CFIR), which is the preferred framework used within the VHA health system [35].

### Data management

All study data will be captured and stored within the VHA using standard tools available to VHA researchers. Information captured from veterans or extracted from medical records will be stored in a secure study database hosted on a password-protected server accessible only to authorized study personnel. The randomization status for each cluster will be kept in a secure location accessible only to study investigators but not the RAs and project managers to ensure blinding.

The database will contain separate tables that will store individuals’ data pertaining to eligibility, enrollment, activation (e.g., non-VHA acute care events), baseline information, 30-day follow up information, 90-day follow up information, and study completion or withdrawal. The database will enable tracking of individuals who are believed to be eligible and whom the study team mailed information about participation, as well as those who met with an RA but were found to be ineligible for study enrollment. This database will be used to drive trial processes as well as store data for planned analyses, both primary and secondary. Periodic review of data completeness and instruments used to capture data will be performed by the study team to ensure quality of data collection and analysis. Furthermore, prompts will be developed in data entry forms for out-of-range and inconsistent entries, to prompt immediate correction.

Informed consent will be obtained from all participants and confidentiality will be ensured. The database as well as hard copies of patients’ informed consent documents and other study files will be secured and stored according to the regulations of the VHA Research & Development Office, institutional ethics board, as well as the Health Insurance Portability and Accountability Act (HIPAA). Study records will be maintained and expunged in accordance with the VHA Records Control Schedule.

Open-ended interview data will be transcribed and coded by VHA research staff. Codebooks will be developed collaboratively by the investigators, and coding quality will be routinely assessed by the study team to ensure consistency across transcripts. Regular meetings to review transcript snippets and coding progress will ensure harmonization of approaches across coders, and disputes will be resolved by the principal investigator.

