**Fig. 3 Fig3:**
[figure not shown]
Screenshot of a non-VA encounter note entered into the VA EHR for a patient in either study arm 1 or arm 2. The note must be acknowledged by a member of the patient’s primary care team

The second intervention, a standardized care transitions intervention facilitated by a geriatric care coordinator, is provided to study patients in arm 2 only. In addition to alerting the PACT team, study coordinators at the two sites provide an electronic notification of the non-VHA acute care event to a geriatric care coordinator. While the background of the care coordinator can vary, both sites used geriatric social workers to fill this role. The care coordinators review the veteran’s medical record in the EHR, and they contact the veteran to schedule an in-home visit within 1–5 days following discharge from the external hospital or ED. If a patient is discharged to a rehabilitation setting, the home visit should occur within 1–5 days after rehabilitation facility discharge.

After the home visit, care coordinators perform at least 3 follow-up phone calls for ongoing education and counseling over the subsequent 30 days. The home visit and any subsequent phone calls are documented in clinical notes within the VA EHR system.

The care transitions intervention follows a standardized model developed by Coleman [16, 17] and focuses on activation of the patient to manage his or her own care. The model consists of four pillars for transition care, including 1) understanding and self-management of VHA and non-VHA medications; 2) diagnosis-specific education and counseling, and understanding “red flag” symptoms that require medical attention; 3) creation of a patient-centered record containing contact information, conditions, medications, and advance directives; and 4) self-management of follow-up care within the VHA and non-VHA systems. Care coordinators consider themselves coaches to facilitate veteran’s active, independent self-management of health rather than passive recipients of service. They prefer that veterans schedule follow-up appointments, resolve medication problems, initiate behavioral changes, and complete rehabilitation exercises themselves. Yet the coordinators emphasize they are available for help and encouragement during the 30-day period.

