Secondary outcome measures were selected to provide information on intermediate outcomes addressed by the HIE and care transitions intervention components. They include:Post-acute care follow up. Timely VHA follow-up will be defined as a follow-up visit with any VHA provider within 30 days of non-VHA hospital discharge or ED visit. Timely phone call will be defined as VHA PACT phone call within 7 days of non-VHA hospital discharge or ED visit. We will obtain VHA encounter and phone call dates from the EHR system, and non-VHA encounter dates will be obtained from the HIE networks.High-risk medication discrepancies, defined as the number of discrepancies in medications classified as high risk for hospitalized older adults, including opioid analgesics, insulin, non-steroidal anti-inflammatory drugs, digoxin, antipsychotics, sedatives/hypnotics, and anticoagulants [25–27]. We will obtain a count of high-risk discrepancies based on medical record review and patient or caregiver interview 30 days after non-VA hospital discharge.Care Transitions Measure. This measure of condition self-knowledge and transitional care quality from the patient’s perspective is ascertained by patient or caregiver interview 30 days after non-VHA hospital discharge. A 3-item questionnaire, previously developed and validated [28], will be used. The questionnaire includes items such as “After I left the hospital, I had all the information I needed to be able to take care of myself” with the response options strongly agree, agree, disagree, strongly disagree, and don’t know.Process measures, which provide information on processes influenced by HIE-notifications and by care transitions intervention components. We will calculate frequency of HIE-access by providers (login percent per encounter; login duration; tabs browsed) through system audits provided by Bronx RHIO and Indiana HIE. We will calculate frequency of veteran contacts (in person and telephone) by PACT team and care transitions coordinator, using EHR chart review and coordinator logs. We will calculate the percentage of care transitions intervention components delivered that were indicated using coordinator logs.

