**Fig. 4 Fig4:**
[figure not shown]
Overview of patient screening, enrollment, and activation procedures performed by research staff. The figure distinguishes between study arm 1 (notification only) and arm 2 (notification plus care transitions intervention)

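### Withholding the PACT allocation list cannot keep research assistants blind at the 90-day abstraction, because arm 2 charts hold the coordinator's notes

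*Protocol article*

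**What the plan says.** All references are to the protocol article.

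- **Data management.** The randomisation status of each cluster is held in a secure place "accessible only to study investigators but not the RAs and project managers to ensure blinding". The article describes no other blinding measure.
- **Data collection methods.** At 90 days, "trained RAs will extract data from the veteran’s electronic medical records to ascertain primary outcomes". On the sources: "The medical records will be obtained from the VHA central data warehouse as well as the Bronx RHIO and Indiana HIE". On the method: "The RAs will use a standardized template for electronic chart review".
- **Participant timeline.** A single chart review of the 90 days after discharge serves both readmission and other secondary outcomes.
- **Interventions.** The care transitions intervention "is provided to study patients in arm 2 only". On its documentation: "The home visit and any subsequent phone calls are documented in clinical notes within the VA EHR system".
- **Outcomes.** Contacts with the veteran by the PACT team and by the care transitions coordinator are a process measure, obtained "using EHR chart review and coordinator logs". The same section presents hospital admission as an objective outcome with little risk of bias.
- **Allocation.** PACTs are assigned to one of the two notification groups, separately by site, and keep that assignment throughout the study.

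**The concern.** The article claims a property, blinding of RAs, and supports it with one measure: they do not see the list. The same RAs later open records in which the arm 2 intervention has been written down. If the claim is meant to cover outcome assessment, the described procedures defeat it.

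A reader of the trial report would then credit a masked assessment of the primary outcome that did not take place. Some judgement does enter that outcome. The abstractor has to reconcile HIE, EHR and warehouse records, identify the index discharge, and move the start of the 90-day window for patients who first go to rehabilitation. An abstractor who knows the arm could resolve doubtful records differently between arms. The count of high-risk medication discrepancies, which draws on record review and interview, leaves more room for this. So does the 30-day interview, in which an arm 2 veteran may simply mention the coordinator's visit.

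**Working it through.** The point rests on no sample size, power or event rate, so there is no figure of the plan to reproduce. The check sets the sections side by side.

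**Step 1. Who assesses the outcome, and from what?** Data collection methods gives the task to RAs and calls it electronic chart review. No step is described that removes note text, fixes the primary outcome before notes are seen, or uses a separate masked abstractor.

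**Step 2. What does the chart contain by then?** Under Interventions, the home visit is planned for 1–5 days after discharge (or after leaving rehabilitation), with at least three calls over the following 30 days, all entered as clinical notes in the VA EHR. An arm 2 patient who received the intervention therefore has these notes on file before the 90-day review. Arm 1 patients have no such notes. The notification note itself appears in both arms 1 and 2, so it does not separate the two randomised arms.

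**Step 3. Can the review avoid those notes?** Not as described. One 90-day review covers readmission and other secondary outcomes (Participant timeline), and coordinator contacts are counted from the chart as well as from logs (Outcomes).

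**Step 4. How far does one disclosure reach?** Each PACT has one arm for the whole study, so an RA who links a coordinator note to its PACT knows the arm of every enrolled patient of that team. The planning figures give the scale:
- Enrolled: 300 per site × 2 sites = 600 (Sample size).
- PACTs: 25 + 41 = 66 (Allocation).
- Enrolled patients with a non-VHA hospital encounter: 25–30% of 600 = 150–180 (Sample size).
- Per PACT: 150/66 = 2.3 to 180/66 = 2.7, before attrition.

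On those figures, spill-over within a PACT typically reaches one or two further reviewed charts. The main route of disclosure is the patient's own chart.

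**Step 5. At which stages can the list work?** Before any non-VHA event there is no coordinator note for that patient. Withholding the list can then keep RAs unaware of the arm while they screen, enrol and complete baseline. It cannot do so at the 90-day abstraction.

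**Result.** The stated measure and the stated procedure are incompatible for the 90-day abstraction, and compatible for enrolment and baseline.

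**The case against.** **The blinding sentence may not concern outcome assessment.** It does not say what the blinding covers. PACTs are allocated before enrolment starts, and hiding the list from the staff who recruit guards against selective recruitment in a cluster trial. This stands: a reader might infer that the blind fails altogether, and the article does not support that. But the sentence sets no limit, and it stands in the section on data capture and storage.

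**The article does not say who counts coordinator contacts.** It could be another person or session, working from the logs. That is fair, so it cannot be said that every abstractor must search for the revealing entries. Still, the chart is a named source for that count, and one review is described for readmission and secondary outcomes together.

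**A structured warehouse extract could preserve the blind, and a condensed article may leave such detail to the full protocol.** Both are possible. Silence on masking procedures would be no finding. Here, however, the article asserts blinding and describes a procedure that does not deliver it.

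**Admission is a hard endpoint.** It comes from several sources, on a standard template, with periodic recoding and retraining. This stands and limits the consequence for the primary outcome.

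Three stronger readings are tempting but not supported:
- *A numerical bias.* A reader might take the 95% chart accuracy as sensitivity for admissions and compare it with a lower value in the other arm. The 95% is a retraining trigger for coding accuracy per chart, and any value for the other arm would be invented. The result would only return its inputs.
- *RAs carry out the arm-specific activation.* The Fig. 4 caption reads "Overview of patient screening, enrollment, and activation procedures performed by research staff". It names research staff, not RAs, and Interventions assigns sending the notification to study coordinators.
- *The usual-care charts break the blind.* Arm 3 is identified retrospectively and is not a randomised cluster group, so its lack of notification notes does not contradict a sentence about cluster randomisation status.

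**Conclusion.** The concern holds for the 90-day abstraction: withholding the list does not blind RAs who review charts in which the arm 2 intervention is recorded. It does not extend to enrolment and baseline, where the list may work as intended.

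The size of any bias cannot be derived from the document. For the primary outcome it is probably modest. It would be larger, if present, for medication discrepancies and the 30-day interview. The conclusion assumes that chart review means access to clinical notes, which is its ordinary sense and the only one that fits counting coordinator contacts from the EHR. If the full protocol specifies a note-free extract for the primary outcome, what remains is to say so in the article.

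**What to change.** 1. **Primary outcome first.** Determine the index discharge date and 90-day admission (yes/no) from encounter-level VHA warehouse and HIE records, which the study already obtains, with arm, PACT and clinical notes not shown. Lock both variables.
2. **Fallback for rehabilitation.** Encounter data may not date discharge home from rehabilitation. In those cases, use a limited extract with coordinator and notification notes withheld.
3. **Notes afterwards.** Only then abstract coordinator contacts, other process measures and the remaining note-based items.
4. **Reword Data management.** State who is masked, for which assessments and until when. For example: RAs are not given cluster allocation during screening, enrolment and baseline; index discharge date and 90-day admission are determined and locked without sight of arm, PACT or clinical notes; RAs who abstract note-based or process measures cannot be assumed blinded.

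The cost is some programming and a re-ordering of the abstraction, plus a few encounters to settle from the fallback extract. No new data source is needed. If the order of abstraction can no longer be changed, the minimum is to correct the sentence so that it does not imply masked outcome assessment.

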### Statistical methods

All analyses will be performed as intention-to-treat (ITT), i.e. all outcomes will be included on patients assigned to treatment groups, even if they deviate from the group’s intervention. We will use a generalized linear mixed (GLM) model to test the effect on the primary outcome of 90-day hospital admission or readmission (e.g., 0 = no, 1 = yes). The logit link of the binary outcome for each observation will be modeled as a linear model, with the PACT team used as a random effect and group assignment (e.g., 0 = notification only or no notification, 1 = notification-plus-coordination) as a fixed effect. Inclusion of random effects in the model accounts for possible within-cluster correlation of the outcome since patients will be clustered by PACT.

To estimate the intervention effect after accounting for patient characteristics, especially those found to be imbalanced between study arms from the preliminary analyses, other covariates will be added as fixed effects to the model. These covariates may include: age, gender, non-VHA hospital, number of pre-admission medications, chronic illness count, discharge diagnosis, and length of stay for the index admission (with ED visits coded as 0 days). In addition to bias reduction, this analysis may increase the power for detecting the intervention effect by reducing the unexplained variance of the outcome and add insight into factors that predispose these patients to the outcome.

A similar approach will be used to test the intervention effect on secondary outcomes. For each secondary outcome, an appropriate distribution or link function will be chosen for the GLM model, e.g. logit link for the binary outcome of scheduled follow-up, Poisson or Negative Binomial distribution for the counts of high-risk medication discrepancies, identity or other links for Care Transitions Measure depending on the distribution of scores.

All analyses will be carried out using the most recent version of SAS (Carey, North Carolina, USA) available to VHA researchers using the VHA computing environment. For all tests, we will use 2-sided *p*-values with alpha = < 0.05 level of significance. Qualitative coding and analysis will be conducted using the most recent version of NVivo (QSR International; Doncaster, Victoria, Australia).

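### The stated primary model leaves out site, the randomisation stratifier, and the adjusted model chooses covariates by observed imbalance

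*Protocol article*

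**What the plan says.** **Randomisation (Allocation).** PACTs are assigned 1:1 from computer-generated lists, "with separate lists for the Bronx VA and Indianapolis VA, in order to maintain balance in groups within each study site". The section gives the cluster counts: "There are 25 primary care PACTs in the Bronx and 41 in Indianapolis".

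**Primary model (Statistical methods).** 90-day admission or readmission is modelled "with the PACT team used as a random effect and group assignment" as the one fixed effect, coded "0 = notification only or no notification, 1 = notification-plus-coordination". There is no site term. The reference category pools the randomised notification-only arm with the no-notification controls. The Trial design and Discussion sections describe those controls as identified retrospectively, from veterans who did not enrol or whose event fell outside the monitoring period.

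**Adjusted model (same section).** Covariates are then added, "especially those found to be imbalanced between study arms from the preliminary analyses". The candidate list is open. It names age, gender, non-VHA hospital, number of medications, chronic illness count, discharge diagnosis and index length of stay. Site is not on it.

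**The concern.** An analysis should reflect the restrictions imposed by its randomisation. Separate lists per site largely remove the site difference from the randomised contrast. A model without site still counts that difference as noise. A PACT random effect does not replace a site term: it treats all 66 teams as draws from one distribution, so a gap between two fixed sites appears as extra variance between teams.

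The protocol gives some reason to think the sites may differ. They use different HIE networks to detect events and outcomes, the centres differ in size, and the GRACE exclusion refers to a programme at Indianapolis only.

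For the retrospective controls the problem is different. They were not randomised, so their site mix can differ from that of the enrolled arms, and a site gap can then enter the group estimate as bias.

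Choosing covariates by observed imbalance makes the adjusted estimate depend on the data in hand. Imbalance between arms is also a poor guide to which variables predict readmission.

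**Working it through.** The protocol gives no between-site difference, so there is no stated figure to reproduce on this point. The gaps below are assumptions, shown as a range.

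**Inputs from the protocol.** 25 + 41 = 66 PACTs (Allocation). From Sample size: 7 subjects per PACT, ICC 0.05, readmission 40% v 26%, total 466. As a check, 466 / 66 = 7.06, which agrees with 7 per PACT. The design effect is 1 + (7 - 1) x 0.05 = 1.30.

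**Randomised events.** The 466 includes the retrospective controls. Enrolment of 600 with 25-30% having events gives 150-180 randomised events before attrition. The midpoint is 165, or 165 / 66 = 2.5 per PACT. Both cluster sizes are therefore shown.

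**Effect on the standard error (linear approximation on PACT proportions)**

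- Variance of a PACT proportion within site: Vw = mean of p(1 - p) x [1 + (m - 1) x 0.05] / m
- Extra variance if site is omitted: Vs = (25/66) x (41/66) x gap² = 0.2353 x gap²
- SE ratio = √(1 + Vs/Vw)

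Site rates are centred on 40%, with the Bronx the higher.

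| Events per PACT | Site rates | Mean p(1 - p) | Vw | Vs | SE ratio |
|---|---|---|---|---|---|
| 7 | 45% v 35% | 0.2351 | 0.0437 | 0.0024 | 1.027 |
| 7 | 50% v 30% | 0.2252 | 0.0418 | 0.0094 | 1.107 |
| 2.5 | 45% v 35% | 0.2351 | 0.1011 | 0.0024 | 1.012 |
| 2.5 | 50% v 30% | 0.2252 | 0.0968 | 0.0094 | 1.047 |

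These rows are under no treatment effect. With a 14-point effect in half the PACTs, mean p(1 - p) falls to 0.2096 and 0.1980, and the four ratios become 1.030, 1.121, 1.013 and 1.054. With a gap of zero, Vs = 0 and the ratio is 1.

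**Simulation.** Stratified cluster trials with beta-binomial PACT rates, analysed by regression of PACT proportions with and without site, agree with this.

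- 7 events per PACT: SE inflation is about 3% at 10 points and 11-12% at 20. Power for a 14-point effect is about 79% without site v 81% with it at 10 points, and 75% v 83% at 20. With Indianapolis as the higher site, the 20-point figures are about 72% v 81%.
- Type I error without site at a 20-point gap is about 3-4% instead of 5%.
- 165 randomised events: SE inflation is about 1% and 5-6%. Power is about 43% v 43% and 42% v 46%.

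**Possible bias through the retrospective controls.** Assume they are half of the comparator and the enrolled arms are split 50/50 by site (300 are to be enrolled at each). The crude shift is 0.5 x (control site share - 0.5) x gap.

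- Share 60%, gap 5 points: 0.5 x 0.10 x 5 = 0.25 points
- Share 80%, gap 20 points: 0.5 x 0.30 x 20 = 3 points

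The shift scales with the controls' share of the comparator. The PACT random effect may absorb part of it where controls and enrolled patients share teams.

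**Who has baseline function and cognition data.** The baseline questionnaire is given to enrolled veterans. Of 466 events, 150-180 (32-39%) would come from enrolled patients. After 10-15% attrition this is 128-162 (27-35%).

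**The case against.** **The effect may be small.** This stands. No site gap is stated, the loss is zero if the sites are alike, and at the likely number of randomised events a 10-point gap costs about 1% in standard error. A 30-point gap would by itself imply a between-site ICC of about 0.2353 x 0.09 / 0.24 = 0.09, above the planned 0.05, so it does not fit the protocol's own assumption. For the randomised contrast the error is in the safe direction for type I error. The calculations also use PACT proportions, not the planned logistic mixed model.

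**Non-VHA hospital could stand in for site.** Partly. It would largely separate the Bronx from Indianapolis, but it is optional and not in the primary model.

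**A SAP may settle the covariates.** That is fair for the final list, which is open. It does not answer the primary model that is written out without site, or the stated preference for imbalanced covariates.

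A reader might infer three stronger points that the protocol does not support:

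- *Baseline function and cognition are ignored.* ADL, IADL and SPMSQ are not named, but the list is open. Most retrospective controls would have no baseline questionnaire, so the pooled model could not use these scores for most patients.
- *The notification is sent at admission, so length of stay and discharge diagnosis are affected by it.* The Interventions section says only that an ADT message follows use of acute care, after which a coordinator enters a note. Notification before discharge is possible but not stated.
- *Those two variables must therefore be removed.* Both are fixed by index discharge, before the home visit and the 90-day window, and both randomised arms receive the same note. Against the non-randomised controls, index severity is a plausible confounder, so dropping it is a trade-off.

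**Conclusion.** The point holds in limited form. The primary model does not carry the stratifier used in the randomisation, and the adjusted model has a data-driven selection rule. Omitting site does not invalidate the randomised comparison. It makes that comparison conservative, by an amount between nothing and roughly a tenth of the standard error for assumed gaps of 0 to 20 points, and by about half of that or less at the expected number of randomised events. Contrasts that include the retrospective controls could shift by about 0.25 to 3 percentage points under the assumed site mixes and gaps. All these sizes rest on assumed site differences. The mismatch between allocation and model does not.

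**What to change.** 1. Add site (Bronx or Indianapolis) as a fixed effect in the primary model and in all secondary-outcome models, keeping the PACT random effect. This costs one degree of freedom and needs no new data.
2. Replace selection by observed imbalance with a covariate set named before outcome data are examined, chosen for expected prognostic value from variables available in all arms. Age, gender, chronic illness count and number of pre-admission medications are already on the candidate list.
3. If ADL, IADL and SPMSQ are to be used, restrict them to the randomised comparison of notification plus coordination with notification only, where baseline questionnaires exist.
4. At most, report comparisons with un-notified controls with and without length of stay and discharge diagnosis, as a sensitivity analysis.

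The cost is a change of wording in the Statistical methods section, plus one extra run if the sensitivity analysis is kept.
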